### Sample

The population will include patients with a diagnosis of HF who will be admitted to a cardiac rehabilitation program in the city of Santiago de Cali, Colombia. It should be noted that this study aims to compare quantitative variables. Studies that compare means use the standard deviation as a measure of variation, so the variable of interest will be the distance covered in meters in the 6-minute walk test (6MWT).

The hypothesis of this study proposes that the group receiving telerehabilitation, telephone follow-up, and education will achieve better results in patients’ aerobic capacity, compared to the other experimental groups.

There are no studies with similar characteristics with telephone follow-up to obtain a walking distance equal to that of the telerehabilitation group. This is because the groups are homogeneous at the beginning of the intervention but heterogeneous at the end of the intervention program; 378.5 ± 96.9 for the conventional outpatient cardiac rehabilitation group and 432 ± 83 for cardiac telerehabilitation).

In turn, 95% confidence is estimated, error α: 5% (0.05), error β: 20% (0.20), power: 1-β: 80%, giving n = 46 participants for each experimental group, which is increased by 12% for possible problems in the measurements or dropouts of the study participants, so that n = 52 will be required and a total of 156 patients with HF per experimental group at the end of the study.

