#### Independent variables.

The variables considered will be age, sex, marital status, health system, occupation, level of education, and socioeconomic strata (in Colombia, strata 1, 2, and 3 correspond to low strata, which include users with fewer resources who are beneficiaries of public utility subsidies. Strata 4, 5, and 6 correspond to high strata, which include users with more significant economic resources), sessions completed, weeks in the program, and percentage of adherence.

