### Data collection, management, and analysis

The information obtained will be recorded in a Microsoft Office Excel 2010 database and exported for statistical analysis to the Statistical Software for Data Science (Stata) V.16. A description of the outcome variables and the population characteristics will be carried out to display the statistical behavior of these variables. Qualitative variables will be presented as frequencies and percentages, while quantitative variables will undergo the Kolmogorov-Smirnov test to determine whether their behavior is parametric or non-parametric.

If parametricity is confirmed, a Levene’s test for equality of variances will be conducted. Once parametricity is established, a paired t-test will be performed to compare pre- and post-intervention results for each group. For non-parametric behavior, the Wilcoxon test will be used, and variables will be presented as medians and interquartile ranges. Additionally, comparisons of the three experimental groups will be made at the start and end of the intervention. If the variables exhibit parametric behavior, a one-way ANOVA test will be used, followed by post hoc tests. For parametric variables with equal variances, the Tukey test will be applied (adjusting for unbalanced groups with Dunnett’s T3 test). If equal variances are not assumed, Dunnett’s T3 test will be used. For non-parametric variables, the Kruskal-Wallis test will be employed. A significance level of 95% will be considered, with a p-value < 0.05 regarded as statistically significant.

An analysis of covariance (ANCOVA) regression model will be used to evaluate the main effect of the outcome variable among the three experimental groups, adjusting for age, sex, and other potential confounding factors (those statistically significant at the 5% level).

A logistic regression model will be considered to analyze a binary outcome (e.g., adherence to recommendations provided through telephone follow-up), utilizing Akaike’s information criterion to select the best model based on its bias and variance.

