Regarding the frequency and duration of the telerehabilitation program, significant differences in the duration of the program in weeks are observed among the different studies, with periods ranging from 8 to 18 weeks, according to the literature on the subject [8,19,20,25,26]. This study defines a 12-week intervention program with sessions scheduled three times per week. This approach is similar to previous clinical trials, which suggest a frequency of intervention between 3 and 5 times per week [8,19,20,22,24]; moreover, it is consistent with the cardiac rehabilitation sessions generally prescribed in Colombia [6].

Concerning exercise prescription, the session is divided into three main phases: warm-up, core training, and cool-down. Concerning intensity, a range of 50% to 70% of HRmax and a value of 11–13/20 according to the conventional Borg scale are established. These results are congruent with those reported in other telerehabilitation studies for patients with HF [8,23–25] and reflect appropriate exercise prescriptions for patients and replication of the study. In addition, to track and monitor the prescription in this study, patients are given an FT4 fleece belt and a digital blood pressure monitor, similar to some studies in which patients were given digital devices to monitor vital signs [9,10,12,17,18] or taught how to take their vital signs [14].

Mobile technology in healthcare allows assessment, measurement, intervention, and remote follow-up synchronously or asynchronously, enabling its application in CR, improving cost-effectiveness, time and interaction with patients, and treatment adherence [27]. Studies involving telephone follow-up have generally been conducted in conventional outpatient rehabilitation programs or at home [28–30], This study aims to provide further insights into cardiac telerehabilitation programs for patients with HF. It demonstrates positive effects on quality of life, reductions in stress and depression levels, and improvements in treatment adherence, thereby facilitating the achievement of therapeutic goals, similar to what was presented in other studies [27,31].

Some limitations of this study include the potential dropout of patients from any of the three groups due to personal or health-related factors, especially in the conventional rehabilitation group, where patients are required to travel to the rehabilitation clinic.

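### The ANCOVA admits any covariate significant at 5% and does not exclude sessions, weeks and adherence, which arise after randomisation and could bias the adjusted arm comparison

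*Protocol article*

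**What the plan says.** In the protocol article, under Data collection, management, and analysis, the purpose of the ANCOVA is stated first: it "will be used to evaluate the main effect of the outcome variable among the three experimental groups". On the choice of covariates, the plan then describes the model as "adjusting for age, sex, and other potential confounding factors (those statistically significant at the 5% level"). Age and sex are therefore fixed, and anything else enters on a significance test. The text does not say what is tested against what, and it does not restrict the candidates to variables measured before allocation.

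The only list of independent variables is under that heading in the outcomes section. It opens with baseline characteristics: "The variables considered will be age, sex, marital status, health system, occupation, level of education, and socioeconomic strata". It closes with "sessions completed, weeks in the program, and percentage of adherence". The two kinds of variable are not distinguished.

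The Discussion expects the second kind to respond to the arm. Writing about telephone follow-up and telerehabilitation, it speaks of "improvements in treatment adherence, thereby facilitating the achievement of therapeutic goals". It also expects dropout "especially in the conventional rehabilitation group, where patients are required to travel to the rehabilitation clinic".

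The same analysis section plans an unadjusted comparison of the three arms at the end of the intervention, by one-way ANOVA or Kruskal-Wallis.

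**The concern.** Randomisation protects a comparison adjusted for baseline variables. It does not protect one adjusted for something the arm itself can change. Sessions attended, weeks completed and percentage adherence are partly results of the allocated programme, so adjusting for them removes whatever part of the effect runs through them. They also reflect disease severity: the article withdraws patients whose symptoms or vital signs interfere with exercise. Severity affects walking distance as well. Conditioning on adherence can therefore create an arm difference where none exists.

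The 5% rule adds to this. A variable related to walking distance tends to pass such a test, so the rule favours exactly the variables that do the damage. An analyst who takes the list of independent variables as the candidate pool, which is a natural reading because it begins with the two fixed covariates, could fit such a model without departing from the text.

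**Working it through.** **The plan's own figure.** The Sample section gives "378.5 ± 96.9 for the conventional outpatient cardiac rehabilitation group and 432 ± 83 for cardiac telerehabilitation" (metres in the 6-minute walk test, 6MWT) and "95% confidence is estimated, error α: 5% (0.05), error β: 20% (0.20), power: 1-β: 80"%.

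- Difference: 432 − 378.5 = 53.5 m.
- Pooled SD: √[(96.9² + 83²)/2] = 90.2 m.
- n per arm: 2 × (1.96 + 0.842)² × 90.2² / 53.5² = 44.6, so 45. The t-based version gives 45.6, so 46, as stated. This is two-sided and unadjusted.
- Dropout: 46 × 1.12 = 51.5, so 52.

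**Assumptions not in the documents.** Mean adherence differs by 15 points between two arms; its within-arm SD is 20 points; a share p of the 53.5 m runs through adherence. Two arms of 46 are compared.

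**If adherence is always included.**

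- Adjusted estimate = (1 − p) × 53.5 m.
- Adherence slope × SD = p × 53.5 × 20/15 = 71.3p m, so residual SD = √[90.2² − (71.3p)²].
- Variance inflation from the arm–adherence correlation = 1 + 15²/(4 × 20²) = 1.14.
- SE = residual SD × √(2/46) × √1.14.

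| Share p | Estimate (m) | Residual SD | SE | Estimate/SE | Power |
|---|---|---|---|---|---|
| 25% | 40.1 | 88.4 | 19.7 | 2.04 | about 0.52 |
| 50% | 26.8 | 82.8 | 18.4 | 1.45 | about 0.30 |
| 75% | 13.4 | 72.6 | 16.2 | 0.83 | about 0.13 |

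**If adherence enters only when p < 0.05 (simulation).**

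| Share p | Adherence admitted | Mean estimate (m) | Power |
|---|---|---|---|
| 25% | about 47% | 44 | 0.62 |
| 50% | about 98% | 27 | 0.30 |
| 75% | about 100% | 13 | 0.13 |

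Only the 25% case changes materially. Unadjusted power is 0.80 throughout.

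**Varying the adherence gap, 5% rule applied.** With a gap of 0.5 SD the mean estimates are about 42, 27 and 13.5 m; with 1 SD they are about 46, 30 and 13 m.

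**No true effect, but a shared cause.** If an unmeasured factor gives adherence and distance a within-arm correlation r, the adjusted estimate is −r × (90.2/20) × 15 = −67.65r m.

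- r = 0.1: −6.8 m; r = 0.2: −13.5 m; r = 0.3: −20.3 m.
- At r = 0.3 the residual SD is 90.2 × √(1 − 0.09) = 86.0 m, the SE is 19.2 m, and about 18% of trials are falsely significant.
- With the 5% rule applied, adherence is admitted in about 83% of trials. The mean estimate is about −19 m and false positives stay at about 18%.

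**Can a true effect change sign?** Combine both mechanisms at r = 0.3, adherence included: (1 − p) × 53.5 − 20.3 gives +33, +20, +6 and −7 m for p = 0, 25, 50 and 75%. Reversal needs heavy mediation and a shared cause together.

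**Selection among true baseline covariates only.** Three arms of 46 were simulated under no effect, with 5 or 10 baseline candidates. Type I error was 0.049 to 0.054 when selecting on association with the outcome, and 0.036 to 0.050 when selecting on imbalance between arms.

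**The case against.** The link between the two sections is inferred. The analysis section speaks of potential confounders, and a variable caused by the arm is a mediator, so a careful analyst would leave adherence out. The independent-variables list may be purely descriptive, and the clinical variables section supplies ordinary baseline candidates such as ejection fraction and lipids. Where the analysis section does name adherence (to the recommendations given by telephone), it treats it as an outcome of a logistic model. All of this stands, and it makes the problem conditional. It does not remove it: the text sets a rule for admitting covariates, sets no baseline limit, and excludes nothing.

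Three stronger readings are tempting, and the document does not support them.

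- **The trial's headline result is at risk.** The ANCOVA is not labelled primary. The sample size rests on an unadjusted comparison, and the unadjusted ANOVA or Kruskal-Wallis test is planned as well.
- **Adjustment would reverse the treatment effect.** At the assumed values a true effect changes sign only when about three quarters of it is mediated and a shared cause is also present.
- **Selection by p-value in itself produces standard errors that are seriously too small.** Among true baseline covariates the type I error stays close to 5%. The cost is a model that depends on the data.

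A condensed article may also leave the full covariate list to an analysis plan. The point is therefore not that the list is absent, but that the rule printed in its place is a poor one.

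**Conclusion.** The point holds as a should-fix. As written, the rule allows variables measured after randomisation into the adjusted arm comparison, and the article itself expects those variables to differ by arm. If they enter, the estimate is not the effect of the randomised programme. The shrinkage can be large: to about half of 53.5 m when half the effect runs through adherence, with power near 0.30. A spurious difference of about -19 m is possible when there is no effect. These sizes rest on an assumed adherence gap, mediated share and shared-cause correlation, none of which the article gives. The direction of the problem does not depend on the exact values; its size does. The planned unadjusted comparison is untouched, but no rule says which analysis prevails if the two disagree.

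**What to change.** In the analysis section, replace the wording "adjusting for age, sex, and other potential confounding factors (those statistically significant at the 5% level") with a fixed set of baseline covariates: the baseline value of the outcome (baseline 6MWT for walking distance), age and sex. Any further baseline variable should be named in advance, and neither significance with the outcome nor baseline imbalance should decide entry.

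Add one sentence: sessions completed, weeks in the program and percentage of adherence are not covariates in any comparison between arms, and are reported by arm or in a separately labelled mediation analysis.

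The cost is two sentences. Baseline 6MWT is already collected before enrolment, the sample size does not change, and no new data are needed. Recruitment ended on 30/01/2025 and completion was planned for 20/06/2025, so the covariates should be fixed before data are analysed by arm.

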## Abstract

**Background:**

Heart failure is a primary non-communicable disease in Latin America and the Caribbean, which significantly reduces patients’ quality of life. After diagnosis, emphasis is placed on cardiac rehabilitation and patient education regarding healthy lifestyles and habits. Interdisciplinary management is crucial in this process. However, lack of treatment adherence is a recurring issue in this population. In this context, technology allows us to address non-adherence to treatment. Its implementation helps overcome barriers and achieve treatment goals.

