#### Telerehabilitation.

The program will be assisted by virtual technology. It will consist of performing exercises at home for 60 minutes three times a week for 12 weeks. The schedules for the telerehabilitation sessions will be agreed with the patients for their full participation. The exercises will be structured as follows: Warm-up, upper and lower limb muscle strengthening, continuous aerobic exercise, and return to rest. A cardiac and pulmonary rehabilitation physiotherapist will monitor the exercises via the Google Meet platform. This intervention will be carried out by experimental groups 1 and 3.

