#### Telephone follow-up.

Telephone calls will be made three times per week (on days other than those assigned for telerehabilitation) as a follow-up method to obtain information from each person on heart rate and perceived exertion during home activities that they will be encouraged to perform outside of the intervention days. This intervention will be carried out by experimental group 1.

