#### Conventional outpatient rehabilitation.

The program will be carried out in the cardiac rehabilitation program of the clinic. It will consist of physical exercises supervised by a physiotherapist specialized in cardiac and pulmonary rehabilitation for 60 minutes, three times a week for 12 weeks, structured as follows: warm-up, strengthening of upper and lower limbs, continuous aerobic training, and return to rest. This intervention will be carried out by experimental group 2.

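### Attendance variables that arise after randomisation are classed as independent variables and could enter the 6MWT ANCOVA, while the only example outcome for the logistic model exists in Group 1 alone

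*Protocol article*

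**What the plan says.** **Logistic model.** Under Data collection, management, and analysis, the article says that a logistic model will be considered for a binary outcome and gives one example: "adherence to recommendations provided through telephone follow-up". Akaike's criterion selects the model. No other binary outcome is named, and the sentence does not mention the arms.

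**Who receives calls.** Table 1 marks telephone follow-up for Experimental Group 1 only. The Telephone follow-up section agrees: "This intervention will be carried out by experimental group 1". The calls are made "to obtain information from each person on heart rate and perceived exertion during home activities that they will be encouraged to perform".

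**Where attendance is placed.** The Independent variables section lists "sessions completed, weeks in the program, and percentage of adherence" beside age, sex, occupation, education and similar characteristics. The list is not restricted to one arm. None of the outcome sections includes adherence.

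**ANCOVA.** The analysis section adjusts the three-group comparison for age, sex and any further possible confounder that reaches 5% significance. It does not say that covariates must be measured before randomisation.

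**Schedule.** Telerehabilitation (Groups 1 and 3) means "performing exercises at home for 60 minutes three times a week for 12 weeks". Conventional rehabilitation (Group 2) runs "for 60 minutes, three times a week for 12 weeks, structured as follows".

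**Role of adherence.** The Abstract states that "lack of treatment adherence is a recurring issue in this population" and presents technology as a way to address it. The Objective section does not list adherence. The Discussion speaks of improved treatment adherence.

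**The concern.** There are two linked problems.

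The first is narrow. Patients in Groups 2 and 3 receive no calls, so they have no value for adherence to advice given in calls. Used as a logistic outcome, this variable can at most describe which Group 1 patients follow the advice. It cannot show whether calls or telerehabilitation change adherence.

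The second bears on the main outcome. Sessions attended, weeks in the program and percentage adherence are observed during the intervention, so the assigned arm can affect them. The article itself expects this: the Abstract says technology helps with non-adherence, and the Discussion expects dropout especially in the conventional arm, because of travel. Variables affected by treatment are not confounders of a randomised comparison. Yet they share one list with baseline characteristics, and the ANCOVA rule selects by p-value. Attendance plausibly correlates with walking distance, so it could pass the 5% screen. Adjusting for it would remove whatever part of the arm effect on 6MWT distance runs through attendance, and the randomised total effect would no longer be what is estimated.

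**Working it through.** **1. The plan's own sample size (Sample section).** Inputs are 378.5 (SD 96.9) m and 432 (SD 83) m, alpha 0.05 (two-sided assumed) and power 80%.

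- Difference: 432 − 378.5 = 53.5 m. Average SD: √[(96.9² + 83²)/2] = 90.2 m.
- Normal approximation: n = (96.9² + 83²)(1.96 + 0.84)²/53.5² = 44.6, so 45 per arm. The t-test version gives 45.6, so 46, which is the stated figure.
- 46 × 1.12 = 51.5, so 52 per arm. Then 3 × 52 = 156, which I read as the trial total.

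The point does not depend on this result. It supplies the 52, the 156 and the 53.5 m used below.

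**2. Can the example outcome carry an arm effect?** Take a logistic model with an intercept and two arm indicators.

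| Outcome defined in | Patients | Rank of design matrix |
|---|---|---|
| Group 1 only | 52 | 1 of 3 |
| All three arms | 156 | 3 of 3 |

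With Group 1 only, both indicators are zero for every patient and no arm contrast can be estimated. An outcome defined in all arms restores it.

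**3. Is there a common measure?** Each arm has 3 sessions per week × 12 weeks = 36 scheduled sessions. Percentage adherence is recorded without restriction by arm. I assume that it refers to these exercise sessions.

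**4. What could adjustment for attendance cost the 6MWT comparison?** The article does not say how much of the effect runs through attendance, so the shares here are assumptions. The standard error with 46 per arm is 90.2 × √(2/46) = 18.8 m. Power is Φ(difference/18.8 − 1.96).

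| Share through attendance (assumed) | Metres removed | Difference left | Power |
|---|---|---|---|
| 0% | 0 | 53.5 m | 81% |
| 25% | 13.4 | 40.1 m | 57% |
| 50% | 26.8 | 26.8 m | 30% |

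This ignores any gain in precision from the covariate. It is an illustration, not a forecast.

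**5. What could an all-arm adherence comparison show?** The Introduction reports that 40% to 55% of enrolled patients adhere and complete. The comparison rates are assumed. With 52 per arm, the 95% CI half-width is 1.96 × √[(p₁q₁ + p₂q₂)/52]. Power is for a two-sided 5% test with pooled variance under the null.

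| Rates | Half-width (points) | Power |
|---|---|---|
| 55% vs 80% | 17.4 | 78.5% |
| 55% vs 75% | 17.9 | 57.2% |
| 40% vs 65% | 18.6 | 73.0% |

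The half-width is therefore about 17 to 19 points. Such a comparison would detect only large differences and should be reported as an estimate with its interval.

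**The case against.** The strongest reply is that the logistic sentence commits to very little. The outcome is given as an example and the model is only to be considered. The three-group comparisons are assigned to ANOVA or Kruskal-Wallis and to ANCOVA. A model of which Group 1 patients follow telephone advice is feasible and coherent. Adherence is not an objective, and a condensed article may leave an exploratory outcome and its cut-off to a fuller document. All of this stands.

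It rules out a stronger reading that a reader might infer: that the trial's only adherence analysis is a single-arm model and that the planned arm comparison of adherence is impossible. The text does not exclude a dichotomised session measure as another binary outcome. It also does not exclude percentage adherence from the general three-group comparison of quantitative variables.

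A second tempting reading is that the plan prescribes adjustment for adherence. It does not. The ANCOVA sentence names age and sex, and no sentence enters attendance into a model. The risk arises from two stated choices taken together: the label given to the three variables and a covariate rule based on significance, without a limit to baseline measurements.

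That part survives the objection. The classification and the selection rule are both written in the article, so this is not detail left to another document.

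**Conclusion.** The point holds in two limited parts.

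- The example outcome for the logistic model can exist only in Group 1. A model of it uses at most 52 of 156 patients and gives no arm contrast. This is a defect only if an arm comparison is wanted. The Discussion's reference to improved adherence suggests that one may be, but the article does not promise it.
- Three post-randomisation variables are classed as independent, and the ANCOVA rule does not keep them out. Following the text could therefore remove part of the arm effect on the 6MWT. The loss is unknown: about 13 to 27 m of 53.5 m if 25% to 50% of the effect runs through attendance. That range rests wholly on the assumed shares, and on the variables passing the 5% screen.

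The unadjusted 6MWT comparison and the sample size are not affected. The correction is worth making before analysis because it protects the adjusted 6MWT result at almost no cost.

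**What to change.** 1. Move the three attendance variables out of the independent variables and label them post-randomisation outcomes.
2. State that ANCOVA covariates are limited to variables measured before randomisation, and that no attendance or adherence measure may be a covariate in the 6MWT model.
3. If an effect on adherence is to be reported, make adherence to the 36 scheduled exercise sessions the logistic outcome. Define it identically in all three arms, fix the cut-off before the analysts see results by arm, and always retain arm whatever Akaike's criterion selects. Report pairwise differences with 95% intervals.
4. Summarise adherence to call recommendations descriptively within Group 1 only.

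The cost is a few sentences of analysis text. The article already lists the attendance variables for collection, so no new measurement or additional patient is needed.
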